### Secondary outcome measures

Secondary outcomes will be specific anxiety symptoms (STAI-Y), coping skills (CISS questionnaire), depression (EPDS questionnaire) in relation to neurodevelopmental and behavioural scores.

The STAI-Y^31^ is a 40-item self-report questionnaire assessing trait anxiety (20 items) and state anxiety (20 items). Each item is rated on a four-point Likert scale, from 1 (= almost never) to 4 (= almost always), with higher scores indicating greater anxiety.The CISS^32^ is a 48-item self-report questionnaire assessing individual coping styles in response to stress. It evaluates three primary coping dimensions: task-oriented coping, emotion-oriented coping and avoidance-oriented coping. Each item is rated on a five-point Likert scale, from 1 (= not at all) to 5 (= very much), with higher scores indicating greater use of the coping style.The PCL-5^35 36^ is a 20-item self-report questionnaire assessing symptoms of PTSD as defined by the DSM-5. Symptom severity is evaluated across four clusters, namely: intrusion, avoidance, negative alterations in cognition and mood and arousal and reactivity. Each symptom is rated on a five-point Likert scale, from 0 (= not at all) to 4 (= extremely), depending on its severity in the last month. A score above the cut-point score of 31–33 indicates PTSD.The EPDS^33 34^ is a 10-item self-report questionnaire assessing postpartum depression symptoms. Each item is rated 0 to 3 depending on the frequency of symptoms in the last week. Total scores range from 0 to 30, with scores above the cut-off point of 12.5 indicating postpartum depression.The ASQ-3^37^ is a parental questionnaire for children aged 1 month to 5 years 6 months that screens five developmental domains: communication, gross motor, fine motor, problem-solving skills and adaptive skills. Each domain contains six items, rated 10 (=yes), 5 (=sometimes) or 0 (= not yet) by the parent or caregiver depending on their child’s current skills. The ASQ-3 is a recommended screening tool of child development with good psychometric properties.^37 41^

### Covariate measures

Medical, sociodemographic and lifestyle factors will be investigated. The sociodemographic factors collected will be maternal educational level, marital status, support systems (close family, access to medical care, level of geographical isolation, etc.), lifestyle characteristics regarding sleep, alcohol use and smoking and physical activity during pregnancy. We will derive indices of socioeconomic vulnerability from the French National Institute of Statistics and Economic Studies and include them in exploratory socioeconomic analyses. The medical factors collected will be type of CHD, gestational age, echocardiographic characteristics of the fetus (growth, associated cardiac anomalies), timing between first CHD fetal diagnosis and psychological assessments, maternal comorbidities including gestational diabetes, hypertension, placental abnormalities and any history of psychological or neurological symptoms for the mother as well as current and past pharmacological treatments. This information will be extracted from medical records, one semi-directive interview and the information questionnaire. Information on the child will also be collected by medical records and will include prenatal (spontaneous vs assisted reproductive technology, antenatal corticoid use or other neuroprotective therapies), perinatal (c-section birth, gestational age, birth weight, Appearance, Pulse, Grimace, Activity, Respiration (APGAR) score at 5 min, cardiac arrest, any other neonatal complications) and operative variables as well as current neurological diagnoses (ie, epilepsy, stroke, other events).

### Procedures

The inclusion visit at Time 0 will take place at each participating centre during the usual follow-up fetal congenital cardiology consultation after the initial diagnosis of cyanotic CHD. The investigator will inform the participant, answering all questions concerning the aims, the nature of the constraints, the foreseeable risks and the expected benefits of the research.

Figure 1 indicates the study visit collection. At Time 1 (third trimester of pregnancy) after obtaining agreement to participate and signing written consent, a semi-structured psychological interview, lasting about 45 min will be conducted. Three main themes will be investigated: (1) diagnosis of CHD, experience of pregnancy and mental health (ie, post-diagnosis psychological experience, existing family resources); (2) perspectives and projections (ie, how to imagine one’s life after one’s child’s heart surgery) and (3) expectancies towards a maternal mental health intervention in the context of prenatal CHD diagnosis. The prenatal psychological interviews may be conducted on site at each centre before or after a follow-up clinical consultation, or by telehealth in order to facilitate the participation of expectant mothers in the study. Self-report questionnaires assessing psychological state (SCL-90-R), anxiety (STAI-Y) and coping strategies (CISS), as well as an information questionnaire (sociodemographic aspects and lifestyle) will be collected. This information questionnaire will collect information about level of education, employment status, marital status, family situation (living alone or with others, number of children), geographical area of residence and distance between home and maternity hospital, available resources (type of support that can be requested and obtained, whether practical, financial or emotional), lifestyle habits, including smoking, alcohol and drugs, physical activity and sleep quality. The questionnaires take approximately 30 min to complete. The time required to complete all the questionnaires is estimated at around 30 min for the mother and 30 min for the father or co-parent. The total duration of the visit is estimated at between 45 min and 1 hour 15 min for the mothers and 30 min for the co-parent. Participants have the possibility to complete the questionnaires at home, after receiving the instructions.

**Figure 1 F1:**
[figure not shown]
Study visit and data collection schedule. CHD, congenital heart disease; GA, gestational age.

At Time 2 (after surgery, before the child is discharged from hospital), a post-partum depression questionnaire (EPDS), an anxiety questionnaire (STAI-Y) and a coping scale (CISS) will be administered to the participants, at the most convenient time for them. Finally, an information note concerning the child’s next visit will be given to the parents along with parental consent for the child’s participation.

At Time 3, a follow-up consultation will be conducted with mothers and their 12 to 18 months old child. The mother will be offered a psychological state questionnaire (SCL-90-R), an anxiety scale (STAI-Y), a coping scale (CISS) and a post-traumatic stress scale (PCL-5). A neurodevelopmental examination using the standardised ASQ-3 and Bayley-4 tests will be conducted, including an assessment of the child’s behavioural and socio-emotional development, and their neurodevelopment (cognition, language, fine and gross motor skills, as well as psychosocial development). No measures will be collected for the co-parent at Time 3. Figure 2 summarises the measurements.

**Figure 2 F2:**
[figure not shown]
Diagram of variables of interest and their measurement. ASQ-3, Ages and Stages Questionnaire-Third Edition; Bayley-4, Bayley Scales of Infant and Young Child Development, 4th edition; CISS, Coping Inventory for Stressful Situations; EPDS, Edinburgh Postnatal Depression Scale; PCL-5, Posttraumatic Stress Disorder Checklist for DSM-5; SCL-90 R, Symptom Check-List-90 R; STAI-Y, State-Trait Anxiety Inventory.

A referral psychiatrist will be appointed in the associated centres to respond to urgent psychiatric needs (ie, severe pathological levels of anxiety and/or depressive disorders identified on the questionnaires and/or any other situation requiring immediate or urgent clinical care).

To enhance participant inclusion, we rely on the involvement of the medical team who conducts prenatal diagnoses with dedicated consultations. We also benefit from the close involvement of patient organisations such as Petit Cœur de Beurre Association. They support clinical research by communicating with families about our study. Clinical research assistants regularly contact families, which allows for close monitoring of children during cardiology consultations. To make it easier for them to attend appointments, travel expenses can be covered by the family association, thanks to a dedicated budget allocated to the association to help families of children with CHD. In addition, neurocardiac centres already have a joint organisation with cardiological follow-up, which will facilitate patient visits.

### Statistical Plan

#### Sample size and power considerations

Our main objective is to determine the association between the antenatal maternal psychological state score measured by the SCL-90-R and neurodevelopmental outcomes at age 1 measured via the Bayley-4 and the neurodevelopmental state score of children with CHD at age 1. We hypothesise a Pearson correlation of r=0.45 (or R2=0.452= 0.202 for linear regression) between the maternal mental health score and the global cognitive score of children with CHD at age 1. The inclusion of 10 covariates in the multiple linear regression analysis with an increase in R2 of 0.20 requires the inclusion of a total of 72 dyads for a power of 90% and an alpha risk of 5% (NQuery software, ROT4-1). As an attrition rate of 20% is expected (due to different causes such as death of the child, or mother or child drop out), a total of 87 dyads will be included.

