### Aims and hypotheses

#### Main objective

*Aim 1*: To characterise the impact of prenatal maternal psychological distress on neurodevelopmental outcomes at age 1 for children with cyanotic CHD who undergo neonatal open-heart surgery. We hypothesise that a higher level of maternal psychological distress as measured by the Symptom Check-List-90 R (SCL-90-R)^29^ will be associated with lower standardised neurodevelopmental scores as measured using the Bayley Scales of Infant and Young Child Development, Fourth edition (Bayley-4^30^) in children with CHD.

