### Data analysis plan

#### Main objective

The relationship between the score on the SCL-90-R prenatal global mental health self-report questionnaire, taking into account the other factors likely to influence the neurodevelopment score (sociodemographic, medical and psychological factors), and the child’s neurodevelopment score at age 1 on the standardised Bayley-4 test, will be assessed using multiple linear regression after checking the conditions of application. The main explanatory variable will be the SCL-90-R global score and the variable to be explained will be the child’s neurodevelopment score. The multivariate results will be reported using Beta coefficients and LSMEANS (adjusted means) and their 95% CI. The analyses will be conducted using SAS 9.4 and R 4.5.

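### The 72 dyads for 90% power size a 10-df test of the covariate block, not the 1-df test of the maternal-distress coefficient that is the primary analysis

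*Protocol article*

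**What the plan says.** Three places in the protocol article bear on this.

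- **Aims and hypotheses, Main objective (Aim 1).** The hypothesis concerns one predictor: "We hypothesise that a higher level of maternal psychological distress as measured by the Symptom Check-List-90 R (SCL-90-R") will go with lower Bayley-4 scores.
- **Data analysis plan, Main objective.** The analysis is a multiple linear regression that adjusts for sociodemographic, medical and psychological factors. "The main explanatory variable will be the SCL-90-R global score and the variable to be explained will be the child’s neurodevelopment score". The primary outcome section names the global severity index (GSI) as the SCL-90-R indicator and the cognitive score as the Bayley-4 indicator.
- **Sample size and power considerations.** The effect is given as a raw correlation: "We hypothesise a Pearson correlation of r=0.45 (or R2=0.452= 0.202 for linear regression) between the maternal mental health score"; its counterpart is the child's cognitive score (0.452 is 0.45² with the superscript lost). The next sentence opens with "The inclusion of 10 covariates in the multiple linear regression analysis with an increase in R2 of 0.20 requires" and goes on to state 72 dyads, with power 90% and alpha 5%, from nQuery. On losses the paragraph says "As an attrition rate of 20% is expected", and the total becomes 87.

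No other power figure is given for the SCL-90-R coefficient.

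**The concern.** As worded, the R² increase of 0.20 is attached to bringing in ten covariates, while the SCL-90-R already has its own R² of 0.202 in the sentence before. Read literally, the power is for showing that the ten covariates jointly add something once maternal distress is in the model. Aim 1 asks the reverse: does distress add something once the covariates are in the model?

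The two tests have different numerator degrees of freedom (10 against 1) and different increments, so a power figure for one says nothing direct about the other. The only quantitative justification for the primary objective would then describe a hypothesis that the study does not hold as primary. A reader could not tell which adjusted association the study is able to detect.

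**Working it through.** **Inputs from the article.** r = 0.45, so R² = 0.45² = 0.2025 (printed 0.202); increment 0.20; 10 covariates; alpha 5% (taken as two-sided for the single coefficient); power 90%; N = 72; 87 to be included; 20% attrition.

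**Formula.** F test of an R² increment with u tested terms: f² = ΔR² / (1 − R²_full), denominator df = N − p − 1, with p = 11 predictors (SCL-90-R plus 10 covariates), so N − 12. The noncentrality λ is f² times N, or, in a more conservative convention, f² times N reduced for fitted terms.

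**Step 1: reproduce 72.** Base R² 0.2025 (SCL-90-R), ten covariates adding 0.20, u = 10:

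- f² = 0.20 / (1 − 0.2025 − 0.20) = 0.20 / 0.5975 = 0.335
- N = 72: λ = 72 × 0.335 = 24.1, df (10, 60), power 90.5%
- N = 71: power 89.9%

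So N = 72 exactly, with λ = f²N.

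**Step 2: other readings, same convention, 90% power.**

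| Reading | N |
|---|---|
| 10-df block, base R² = 0 | 92 |
| 10-df block, base R² = 0.30 | 62 |
| Overall test of 10 or 11 predictors, R² about 0.20 | 91–96 |
| Overall test of 10 or 11 predictors, R² about 0.40 | 41–43 |
| Simple regression on SCL-90-R alone | 44–45 |
| Pearson r = 0.45, Fisher z | 48 |
| 1-df SCL-90-R coefficient, increment 0.20, covariates explain nothing further | 45 |
| 1-df SCL-90-R coefficient, increment 0.20, covariates explain another 0.20 | 35 |

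For the last two rows, basing λ on N − 10 gives 55 and 44. The 1-df test therefore needs about 35–55 dyads, not 72.

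**Step 3: power that belongs to the primary test.** u = 1, 10 covariates, f² = r_p² / (1 − r_p²), where r_p is the partial correlation of GSI with the Bayley-4 cognitive score. At r_p = 0.45, f² = 0.2025 / 0.7975 = 0.254. Evaluable N is 72 as stated, or 69 if 20% of 87 are lost (87 × 0.8 = 69.6).

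| N | λ based on | Power at r_p = 0.45 | r_p for 90% | r_p for 80% |
|---|---|---|---|---|
| 72 | N | 98.8% | 0.362 | 0.318 |
| 72 | N − 10 | 97.4% | 0.386 | 0.340 |
| 72 | N − 12 | 97.0% | 0.391 | 0.345 |
| 69 | N | 98.4% | 0.369 | 0.325 |
| 69 | N − 10 | 96.8% | 0.394 | 0.348 |
| 69 | N − 12 | 96.2% | 0.400 | 0.353 |

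The last two rows for each N are variants of the conservative convention.

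**Step 4: what confounding could do (assumed inputs, none in the article).** Let the covariates explain a share A of GSI variance and B of Bayley variance, and let c be the correlation between the two covariate-predicted parts. Then r_p = (0.45 − c√(AB)) / √((1 − A)(1 − B)). With A = B = 0.20 and 69 dyads:

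- c = 1 (maximum overlap): r_p = (0.45 − 0.20) / 0.80 = 0.31, power 69–77%
- c = 0.75: r_p = (0.45 − 0.15) / 0.80 = 0.375, power about 85–91%
- c = 0.5: r_p = (0.45 − 0.10) / 0.80 = 0.44, power 95–98%
- c = 0: r_p = 0.45 / 0.80 = 0.56, power above 99%

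**The case against.** The best defence is that nothing about the study has to change. On the article's own effect size, taken as the adjusted effect, 72 dyads give well over 90% power for the right test, and the planned number is larger than that test needs. The design, primary variable and model stay as they are. The analysis section also promises coefficients with 95% confidence intervals, and these, rather than planned power, show which effects a null result leaves open. All of this stands, and it limits the consequence. It does not rescue the sentence, which attaches a specific figure to a specific test that is not the primary one. A fuller protocol or SAP could add a correct calculation, but would not make this one right.

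A reader might go further and infer that the study is underpowered, because Aim 3 expects education, family support and CHD severity to be related to maternal distress. The article does not support that. Aim 3 puts no size on those links and does not concern the Bayley score. Adjustment weakens the distress association only if the same covariates also predict the Bayley score in an aligned direction. The article's Introduction says that socioeconomic factors appear to influence impairment, but again gives no size. Power of 69–77% requires the covariate-predicted parts of GSI and Bayley to be perfectly correlated, which with ten mixed covariates is an upper bound on overlap and not an expected case. At half that alignment, power is back to 95–98%.

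**Conclusion.** The sentence is wrong as written: the 72 dyads and 90% power describe a 10-df test of the covariates, and the maternal-distress coefficient has no stated power. The identification is firm, because both the wording and the number point to the block test and none of the other readings tried gives 72.

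The effect on adequacy is small on the article's own inputs. With r = 0.45 as the partial correlation, two-sided 5% and ten covariates, power is about 97–99% at 72 and 96–98% at 69. What is missing is the threshold: 90% power holds down to a partial correlation of about 0.36–0.39 at 72, or 0.37–0.40 at 69. Whether the true adjusted association lies above that cannot be settled from the article, which gives only an unadjusted value. The ranges reflect the choice of noncentrality convention and nothing else.

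**What to change.** Replace the sentence on ten covariates with a statement for the primary test. For example: *With 72 evaluable dyads, 10 covariates and two-sided alpha 5%, the study has 90% power to detect a partial correlation of about 0.36–0.39 between the SCL-90-R GSI and the Bayley-4 cognitive score (80% for about 0.32–0.34).* If 69 are expected to be evaluable, use 0.37–0.40 and 0.32–0.35. Name the noncentrality convention; once one is chosen, each range becomes a single number. Say that r = 0.45 is an unadjusted value.

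A confounding scenario is optional. If one is shown, label the shared-variance inputs as assumptions, mark the 20%/20% case as a maximum-overlap bound, and give its power under both conventions (69–77% at 69 dyads).

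The cost is one rewritten paragraph, with a less tidy headline figure. Enrolment and the analysis model stay as planned.

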## METHODS AND ANALYSIS

### Study design

This is a national multicentre, non-interventional, prospective and longitudinal study of prenatal maternal mental health and child’s neurodevelopmental outcomes in CHD (n=87 mother-child dyads). Expecting women who consent to participate will undergo psychological evaluations. These evaluations will be conducted by a psychologist with expertise in perinatal mental health. This psychological assessment is conducted at three time points:

Time 1 (T1), during the third trimester of pregnancy (prenatal period), between 28 and 38 weeks of gestation;Time 2 (T2), after the child’s cardiac surgery, and before their hospital discharge (ie, in the postnatal period, after intensive care transfer to inpatient care); andTime 3 (T3), between 12 and 18 months after birth of the child with CHD.

The father or co-parent of the unborn child will also be invited to participate in the study at Time 1 by completing self-report questionnaires similar to those of the expecting participant. The child with CHD will be involved in a neurodevelopmental assessment when he/she is 12–18 months of age. This visit will be integrated into his/her usual cardiac neurodevelopmental care, whenever possible.

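### The 20% attrition allowance is added to 72 instead of dividing 72 by 0.80, so 87 dyads leave 69 to 70 evaluable: a minor arithmetic error that costs about one point of power

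*Protocol article*

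**What the plan says.** All the relevant figures stand in one paragraph of the protocol article, under Sample size and power considerations.

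- Effect size: "We hypothesise a Pearson correlation of r=0.45", which the paragraph converts to an R² of 0.202. It then adds 10 covariates with an R² increase of 0.20.
- Required number: the regression "requires the inclusion of a total of 72 dyads for a power of 90% and an alpha risk of 5" per cent.
- Attrition: "As an attrition rate of 20% is expected". The causes given are death of the child and drop-out of mother or child.
- Recruitment target: "a total of 87 dyads will be included".

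The Abstract and the Study design section repeat the 87 (in the latter, "outcomes in CHD (n=87 mother-child dyads") but make no claim there about attrition or power. The article describes measures to help families attend, but no replacement of lost dyads and no further margin.

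**The concern.** An attrition rate is a share of those enrolled, so the recruitment target is the required number divided by the share that remains. The 87 instead looks like the required number plus 20% of itself, which is always too few.

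The listed causes of loss remove the Bayley-4 score at 12 to 18 months. That score is the dependent variable of the primary regression, so a lost dyad cannot count towards the 72. If the expected attrition occurs, the study ends below the evaluable number that the same paragraph calls necessary, and the stated 90% power is not reached. At stake is the correctness of a headline design figure and a small amount of power.

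**Working it through.** **Inputs, all from Sample size and power considerations.** Required dyads 72; power 90%; alpha 5%; attrition 20%; dyads to be included 87; r = 0.45; 10 covariates; R² increase 0.20.

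**1. Reproduce the 87.** Required number × (1 + attrition) = 72 × 1.20 = 86.4, rounded up to 87. This matches the stated target.

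**2. Apply the attrition to those included.** Required number / (1 − attrition) = 72 / 0.80 = 90. The stated target is 90 − 87 = 3 dyads lower.

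**3. What 87 delivers.** 87 × 0.80 = 69.6, so 69 to 70 evaluable dyads, a shortfall of 2 to 3 against 72.

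**4. Attrition that 87 can absorb.** 1 − 72/87 = 15/87 = 0.172, so 17.2%.

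Steps 1 to 4 need no power model.

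**5. Reproduce the 72.** The article does not say which R² is already in the model before the increase of 0.20. *Assumption:* it is the 0.202 obtained from r = 0.45. Then

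- f² = 0.20 / (1 − 0.202 − 0.20) = 0.20 / 0.598 = 0.3344;
- noncentrality λ = n × 0.3344;
- F test with 10 numerator and n − 12 denominator degrees of freedom (one exposure, 10 covariates, intercept), alpha 0.05.

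| Evaluable dyads | Power |
|---|---|
| 72 | 90.4% |
| 71 | 89.9% |
| 70 | 89.3% |
| 69 | 88.6% |

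So 72 is the smallest number that reaches 90% on this reading, which supports the reading and shows that 72 has no slack. Close variants of the degrees of freedom give a required number of 71 to 73. With a base R² between 0.20 and 0.2025, power is about 88.5% to 88.8% at 69 dyads and 89.1% to 89.4% at 70.

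**6. The single-exposure test.** The Data analysis plan names the SCL-90-R global score as the main explanatory variable, which means a test of one coefficient. *Assumption:* that score explains R² = 0.45² = 0.2025 and the 10 other covariates explain nothing. Then f² = 0.2025 / 0.7975 = 0.2539, with 1 and n − 12 degrees of freedom. Power is 98.4% at 69, 98.6% at 70 and 98.8% at 72. About 45 dyads reach 90%.

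**The case against.** The strongest case on the other side is that this hardly matters, and on size that case stands.

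- The 20% is a rounded planning guess. The difference between 20% and the 17.2% that 87 can absorb is two to three dyads, well inside the uncertainty of such a guess.
- Power falls by only 1.1 points (90.4% to 89.3%) or 1.8 points (90.4% to 88.6%).
- Those power figures rest on a base R² that the article does not state. It is inferred because it returns 72.
- The Abstract and the Study design section are not wrong in giving 87, because they attach no power or attrition statement to it.

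None of this makes the paragraph consistent. Reading the 72 as already covering losses fails, because the next sentence raises it to 87 on account of attrition. Rounding does not turn 90 into 87. Nor is this a detail that a journal article leaves to a fuller document: the article prints all three figures, and they disagree.

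A reader might infer something stronger: that the study is underpowered for its main objective, or that the error must be cured by recruiting more families. The document does not support that. The power that slips below 90% belongs to a test of a block of 10 covariates. At the hypothesised effect, the test of the SCL-90-R coefficient stays near 98% with 69 to 70 dyads, under the assumption in step 6. Whether 72 was derived for the right test is a separate question and does not make this error more serious.

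**Conclusion.** The concern holds as a minor arithmetic error. The attrition allowance was applied as 72 × 1.20 when 72 / 0.80 was needed. The stated attrition leaves 69 to 70 evaluable dyads, 2 to 3 fewer than the paragraph requires, and this conclusion depends only on the article's own three numbers.

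The cost in power is about one point against the stated 90% (88.6% to 89.3%), conditional on the assumed base R² of about 0.20. Aim 1 is not threatened by this error alone, provided that the SCL-90-R effect is as large as hypothesised; the figure of about 98% also assumes that the other covariates explain nothing. The sentence should be corrected because it promises something that its own figures do not deliver, not because the study would fail.

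**What to change.** Correct the last sentence of Sample size and power considerations. Keeping 87 is acceptable if the text then says one of the following:

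- 87 included dyads with 20% attrition leave 69 to 70 evaluable, with about 89% power on the current calculation; or
- 87 included dyads preserve 72 evaluable dyads only for attrition up to about 17%.

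Either wording costs one sentence and changes neither design nor analysis. If the power figure is quoted, the paragraph should also state the base R² that it uses.

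If the sponsor prefers to keep both 20% attrition and 72 evaluable dyads, the target becomes 90. That is three more dyads across five centres. Only in that case do the Abstract and the Study design section need to change.
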